### Description of AI-based communication skills exercise

The intervention component of this trial involves AI-enhanced communication skill exercises specifically designed to foster basic communication abilities using principles from motivational interviewing and other communication frameworks. The exercises utilise a set of system prompts developed to tailor the generative AI to interact with students as intended. Each exercise session begins with the AI mentioning or outlining the motivational interviewing technique, followed by a short vignette or task that students shall respond to by applying the respective or appropriate technique. After students submit their responses, the AI provides feedback based on predetermined criteria that reflect best practices in the respective technique. Students are also encouraged to tailor their interactions with the AI to simulate conversations with specific personas or subjects possessing distinct characteristics or communication needs. This includes the option for language practice beyond German, accommodating a wider range of communication scenarios. Participants are instructed not to provide any personal information within the interactions with the AI.

To facilitate a structured learning experience, students can request example answers from the system. This feature is intended to provide students with model solutions to compare against their responses. Students interact with these prompts through the HAWKI interface, which connects them to advanced language models from OpenAI’s GPT framework. After each set of interactions, students are required to document the exchange by copying the transcript of their conversation with the AI into a designated field on the Stud.IP platform, ensuring that their responses are recorded and assessable.

The curriculum for the intervention includes a series of distinct AI-enhanced communication skills exercises. Students are encouraged to complete each exercise to reinforce their learning and ensure proficiency in the communication skills being trained. During the designated training periods, students may engage in an unlimited number of exercises, allowing for flexible, self-directed learning tailored to their individual needs and schedules. The exercises shall allow repeated practice and receiving iterative feedback from the AI, enhancing the learning process. The students will receive regular notifications to inform them about the next set of exercises that is consecutively made available during the phase at which condition 1 is implemented. This approach is designed to maximise the accessibility and effectiveness of the training, adapting to the diverse learning preferences and requirements of the students.

Currently, HAWKI supports text-based interactions only, and no voice functionality is available within the university’s data-protected wrapper. Therefore, all AI exercises in this study will be text-based for consistency. If future HAWKI updates enable secure audio or multimodal exchanges, we may explore those in a separate follow-up investigation; they will not be part of the main RCT described here.

### Pilot study phase

Before initiating the main trial, we conducted a single-semester pilot study phase (during winter-term 2024/2025) to determine the technical feasibility of the AI-supported exercises, finalise the study instruments, and rehearse all organisational procedures. Voluntary participants from two communication-skills seminars were cluster-randomised to a crossover design: one class followed the sequence AI-enhanced training first, teaching-as-usual (TAU) second, the other TAU first, AI-enhanced training second. Each treatment period lasted 3–4 weeks, with assessments at baseline, mid-seminar, and end-of-seminar. Further, the pilot study phase included students from a non-randomised seminar not receiving the AI-supported exercises. Participation was voluntary and all students provided written informed consent under the same eligibility criteria that apply to the main study, despite the semester at which the seminar took place.

During the pilot we stress-tested the HAWKI platform under routine classroom conditions. We actively sampled transcripts, logged response latencies and flagged any instance in which the AI (i) failed to adopt the instructed patient role, (ii) produced technically or ethically inappropriate feedback, or (iii) deviated from the task instructions. Prompts that did not consistently elicit the intended interactions were iteratively revised or discarded. Only prompts that demonstrated stable performance across all monitored sessions were retained, and we froze this final prompt set for the main trial (changes during the main trial are limited to critical bug-fixes).

The pilot data also served psychometric purposes. We piloted the self-developed communication-skills competence test and refined it where required. Because the pilot’s primary function was developmental, none of its participant-level data will enter the analyses of the main study. Where appropriate, aggregated pilot findings will be reported separately to document feasibility outcomes and instrument refinement.

### AI implementation and monitoring

*AI version.* The HAWKI platform employs current state-of-the-art AI models, currently incorporating the GPT-4o model, version gpt-4o-2024–08-06, as provided by OpenAI as of October 2024. We anticipate changing to new versions throughout the study, following respective releases.

*Prompt management and procedure for acquiring and selecting the input data for the AI intervention.* The initial input data for the AI intervention, preparing the AI for interaction with the trainees, comprise the pretested system prompts designed to guide the AI in facilitating user interactions. These prompts are specifically developed to support exercises aimed at enhancing communication skills, as outlined in the communication skill seminar.

*AI performance surveillance.* While AI outputs were actively monitored and analysed through targeted sampling during a pilot phase during winter-term 2024/2025 (see above), the finalised prompts remain unchanged during the main study, except for critical fixes (e.g., to address system outages). This ensures consistent AI behaviour and feedback for all participants.

*Inclusion and exclusion criteria at input data level.* System prompts are included in the exercise protocol only if during the pilot phase, they consistently elicited the intended user interactions.

*Quality handling procedures.* System prompts that during the pilot phase resulted in interactions of suboptimal quality – for example, the AI failing to assume a patient role or to provide correct task instructions, or where model answers or feedback are inappropriate – were flagged for review or removed from the protocol. This ensures the reliability and efficacy of the training exercises and maintains the quality of outputs from the AI system and shall also improve adherence to the AI training procedure.

*Output of the AI Intervention.* The output of the AI intervention consists of detailed transcripts of interactions between the students and the AI system. These transcripts capture the entirety of the communicative exchanges, providing a comprehensive record of the dialogue, responses, and the feedback generated by the AI.

*Contribution of Output to Clinical Practice and Decision-Making. *The output of the AI intervention is primarily educational and does not directly contribute to clinical decision-making. However, the intervention is designed to enhance the communication skills of psychology students, which is crucial in their professional training and future clinical interactions. By improving these skills, the AI intervention indirectly supports students in making informed decisions and effectively communicating in various future professional settings.

*User access.* Integration of the AI intervention necessitates setting up access to the HAWKI platform, either via devices provided by the university, or from offsite, where participants require a reliable internet connection to access the platform remotely.

*Human-AI Interaction and Required User Expertise.* Human-AI interaction is facilitated primarily through the setup and oversight of the AI operations. The system is designed to be user-friendly, requiring no specific technical expertise beyond proficiency with the online learning platform Stud.IP, which is routinely used in classes at the university. This approach ensures that all users, irrespective of their technical background, can efficiently engage with the AI without extensive training.

### Study outcomes

The primary and secondary outcomes of this study, along with their assessment instruments, time points, and specific variables, are described below and detailed in Table 1.

**Table 1 Tab1:** Assessment instruments

**Construct**	**Original scale**	**Scale translation to German**	**Comments**	**Between-subjects design**			
				**Cluster Type A (AI condition)**		**Cluster Type B/C**^**a**^** (Control group)**	
				**T0**	**T1**	**T0**	**T1**
Sociodemographic characteristics	-	Self-developed		x		x	
Training and experience with AI	-	Self-developed		x		x	
Training and experience with communication skills	-	Self-developed		x		x	
Communication skills competence test (Primary Outcome)	-	Self-developed	The test is being developed during winter-term 2024/25	x	x	x	x
Academic self-concept (regarding communication skills)	Self-Description Questionnaire III [20]	Adapted from Schwanzer et al. [21]	Only the subscale ASC Mathematics, item texts adapted to Communication Skills (approach similar to Simonsmeier et al. [22])	x	x	x	x
Self-efficacy (regarding communication skills)	SE-12 [23]	SE-12-G [24]		x	x	x	x
Attitude Towards AI	AI Attitude Scale [25]	Self-translated, using committee approach		x	x	x	x
Volume of communication skills exercises	-	Self-developed	Total and AI only; student-reported and as registered in the online learning platform Stud.IP		x		x
Student evaluation of the communication skills practice	-	Self-developed			x		x
Motivation (regarding the communication skills practice in the courses)	Intrinsic Motivation Inventory [26, 27]	German translation downloaded from https://selfdeterminationtheory.org/intrinsic-motivation-inventory/			x		x
Student evaluation of course quality	-	*Trierer Inventar zur Lehrevaluation* [28]	Slightly shortened and adapted		x		x
Usability of the technical system (HAWKI + prompt)	System Usability Scale [29]	Rummel [30], as recommended by Brix et al. [31]			x		
Content of communication skills exercises	Motivational Interviewing Treatment Integrity 4.2 [32] scale	Original version used	AI-based exercises, evaluated by AI and human raters using a standardised coding scheme		x		x
Feedback on AI-use in the seminar context	-	Self-developed	Group discussion; only possible if all students from a discussion group agree to participate in the study; recorded for later transcription and analyses		x		

*Abbreviations*: *AI* artificial intelligence, *ASC* academic self-concept, *SE-12* self-efficacy questionnaire, *SE-12 G* German self-efficacy questionnaire

^a^The nonrandomised control condition (Cluster Type C) completes the same measures as the control condition in the randomised Cluster Types

The primary outcome is the change in communication skills from baseline, measured using a set of questions designed to reflect the communication skills emphasised in the training. This outcome will be assessed at two time points: t0 (baseline, before the start of training phase) and t1 (end of seminar, after training phase). The primary outcome will be analysed as a z-standardised change score to evaluate the improvement from baseline to subsequent time points. We use data collected during a study pilot phase during winter-term 2024/25, to pilot the set of questions and adapt the assessment if necessary.

Secondary outcomes include measures related to the participants of the course, the use of AI and the perceived quality of the course, such as attitudes towards AI, self-concept and self-efficacy, motivation, user experience with the AI tool, as well as students’ evaluations and feedback. These outcomes are assessed at various time points throughout the course using a combination of validated scales and self-developed measures, as detailed in Table 1.

Each student’s interaction with the AI-system is recorded and can be analysed using criteria derived from motivational interviewing best practices (Motivational Interviewing Treatment Integrity, MITI, 4.2) [32] by human raters and AI. These assessments focus on the accuracy and appropriateness of the techniques used.

### Data management, confidentiality, and monitoring

Data collection for this study will utilise both online tools and direct assessments. Most data will be collected via the online data collection tool EFS Survey tool (Tivian). Further, content and volume of communication skills exercise will be retrieved from the “Stud.IP” platform. Participants will be asked to provide a personal code that they individually derive and to provide it within EFS Survey and Stud.IP, allowing for later merging of data collected via different platforms. A list linking names and email addresses of participants with the personal codes will be kept separate from all other data in an access-controlled file.

Data confidentiality will be maintained throughout the study. Data from surveys and assessments will be stored digitally using encrypted and password-protected servers. Data will be pseudonymised using unique participant identifiers to ensure that personal information cannot be directly linked to the collected data. Only authorised research team members will have access to the raw data. Data retention will comply with institutional requirements. Any data shared for analysis or publication purposes will be stripped of identifying information to maintain participant privacy. Data validation procedures will include range checks and consistency checks to identify any irregularities.

This study will not have an independent data monitoring committee (DMC) due to its educational research context and relatively low-risk nature. Data oversight will be managed internally by the principal investigator and designated research team members at our institution. In the event of unexpected issues or potential adverse events related to the intervention, a protocol will be in place for prompt reporting and review by the research team.

### Participants, recruitment, randomisation procedures, and sample size estimates

Recruitment for this study will target students enrolled in the communication skill seminar (*Seminar Gesprächsführung*) as part of the Bachelor of Science in Psychology program at a German university.

Inclusion criteria for study participants are as follows: 1) Being enrolled as student in the communication skill seminar (Seminar *Gesprächsführung*, A3), which is part of the Bachelor of Science in Psychology program; 2) Participating in one of the seminars from summer-term 2025 up to winter-term 2025/2026; 3) At least 18 years of age; 4) Sufficient proficiency in the German language to participate (as the seminar is conducted in German, this is implicitly given, as German language proficiency is required for course participation). There are no additional exclusion criteria for this study.

Recruitment for the main study begins summer-term 2025 up to winter-term 2025/2026. Participants will be informed about the study by the seminar teachers. Students will be encouraged to participate voluntarily, with informed consent required for enrolment. Reminder messages will be sent out to maintain interest and promote participation throughout the study duration.

The timeline for participant enrolment, interventions, and assessments is as follows: Enrolment begins early during each semester/course, where students provide informed consent. We provide the current informed consent forms (for classes randomised to Conditions 1 and 2 and one for classes in Condition 3) as additional file 1. Allocation occurs at the start of the course (t0), followed by the baseline assessments. The end of the course (t1) includes final assessments. Data close-out for each semester occurs after t1 with optional group discussions. Final data close-out will occur following the last semester during which new data are collected, and any follow-up assessments are completed.

With regard to target sample size, our goal is to enrol at least 50 participants per condition to ensure robust statistical power for detecting medium effect sizes, allow stratified analyses, and to enhance the generalisability of our findings. During the two semesters contributing to the main study, we anticipate recruiting participants from at least 10 seminars.

Randomisation for the study will be conducted at the seminar level, with each seminar class being randomised according to the scheme outlined in Fig. 1. The randomisation process will be conducted by an independent party to ensure unbiased allocation, using coin-flip or computer-generated randomisation procedures, to determine to which condition (Condition 1 or Condition 2; Cluster Types A and B, respectively) each class is assigned, while a rule is implemented so that, if a given instructor teaches multiple classes in one semester, the difference in the number of classes assigned to Cluster Type A vs. Cluster Type B does not exceed one. Our main comparison focuses on the randomised arms (Cluster Types A and B). Additional non-randomised comparison classes (Condition 3, Cluster Type C) will be included only if a given seminar cannot be randomised due to scheduling or instructor constraints. These observational data serve as ancillary information but will not be part of the main randomisation-based analysis.

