### Allocation concealment/blinding

The blinding strategy for this study includes rater blinding to maintain the integrity of the data and minimise bias. Given the nature of the study, it is not feasible to blind participants to the type of intervention. Raters responsible for evaluating communication skills exercises and correctness of free-text responses will be blinded to the condition to which the participants were assigned. In circumstances where unblinding becomes necessary (e.g., unforeseen technical issues or procedural clarifications), a strict protocol will be followed to disclose the intervention assignment in a controlled manner.

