### Harms

Given the nature of this educational intervention study, no significant physical or psychological risks are anticipated for participants. The potential harms are minimal, primarily related to possible discomfort or stress associated with the exercises or evaluations. To mitigate these risks, participants will be informed that their participation is voluntary and that they may withdraw at any time without any repercussions. Non-participation does not affect potential access to the AI-enhanced skill training; the latter only depends on the class the student is in.

If participants experience significant distress during the intervention or assessments, they will have the option to pause or discontinue their involvement in the study and no further information will be collected. The research team will remain available to address participant concerns and provide support or referrals to appropriate university resources if needed.

All relevant incidents and adverse events will be documented and reviewed by the research team, with a summary provided to the IRB as necessary.

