### Consent or assent

Informed consent will be obtained from all participants before enrolment in the study. The consent process will include an explanation of the study’s purpose, procedures, potential risks and benefits, and the rights of participants, including the right to withdraw at any time without consequences. This information will be provided in written form, and participants will have the opportunity to ask questions before signing the consent form.

The consent forms will be distributed and collected either in person during the initial seminar sessions or electronically through the EFS Survey tool (Tivian), ensuring accessibility for all participants. The form includes details on data privacy, indicating how data will be stored, used, and protected.

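### Classes are allocated before the baseline test and nothing says the arm is withheld until t0 closes, so the t0 half of the primary change score is open to knowledge of the arm

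*Protocol article*

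**What the plan says.** The timeline in *Participants, recruitment, randomisation procedures, and sample size estimates* lists enrolment with consent early in the course, and then: "Allocation occurs at the start of the course (t0), followed by the baseline assessments". The same section has an independent party randomise whole classes.

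*Study outcomes* defines the first time point as "t0 (baseline, before the start of training phase", which places it before training but not before allocation or its announcement. It also makes the t0 score part of the endpoint: "The primary outcome will be analysed as a z-standardised change score to evaluate the improvement from baseline to subsequent time points". Table 1 schedules the competence test, self-concept, self-efficacy and attitude towards AI at both T0 and T1 in both randomised arms.

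On blinding, *Allocation concealment/blinding* states that "it is not feasible to blind participants to the type of intervention". The protection it offers is on the assessor side: "Raters responsible for evaluating communication skills exercises and correctness of free-text responses will be blinded to the condition".

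*Consent or assent* says the forms are "distributed and collected either in person during the initial seminar sessions or electronically through the EFS Survey tool". *Harms* adds: "Non-participation does not affect potential access to the AI-enhanced skill training; the latter only depends on the class the student is in". *Data analyses* plans baseline scores as a covariate.

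**The concern.** In a cluster trial, one announcement tells a whole class its arm. If that happens before t0, students sit the baseline knowing whether they will get the AI exercises, and they may try harder or less hard, or rate themselves differently. Blinded raters do not prevent this, because the reaction lies in the answers and not in the marking.

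A baseline that reacts to allocation is no longer a pre-randomisation measurement. Here it enters the primary analysis twice: it is subtracted from t1 to form the change score, and it is a candidate covariate. Larger classes would not reduce the resulting bias, and no later analysis can recover a baseline that was taken after the arm was known.

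Consent is a secondary matter. If some students sign after the class knows its arm, who joins could also depend on the arm.

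**Working it through.** **1. Order of events.** Consent comes first, then allocation, then the baseline assessments. Students are unblinded. No section places a barrier between allocation and the students' or teacher's knowledge of it before t0 is complete. The independent party covers how the allocation is generated, rater blinding covers the marking, and the definition of t0 covers only its timing relative to training.

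**2. Inputs for the size.**
- From the article: the endpoint is the change from t0; baseline scores are planned as a covariate; at least 50 participants per condition; alpha 0.05 (taken as two-sided, since sidedness is not stated).
- Assumed, because the article gives no figure: an arm difference at t0 of s = 0.1–0.2 SD caused by knowing the arm; a t0–t1 correlation of r = 0.5, with 0.7 as a second case; equal SDs (set to 1) at both time points; no clustering.

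The article states no figure for this effect, so there is none to reproduce.

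**3. Formulas.** Let s be the AI-minus-control shift at t0.
- Shift gone by t1: bias in the change score = 0 − s = −s. With baseline as a covariate, bias ≈ 0 − r × s = −r × s.
- Shift equally present at t1: bias in the change score = s − s = 0. With baseline as a covariate, bias ≈ s − r × s = (1 − r) × s.

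**4. Results (absolute size, in SD of the t0 score).**

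| s | r | Change score, shift gone by t1 | Covariate, shift gone by t1 | Change score, shift persists | Covariate, shift persists |
|---|---|---|---|---|---|
| 0.1 | 0.5 | 0.10 | 0.05 | 0 | 0.05 |
| 0.2 | 0.5 | 0.20 | 0.10 | 0 | 0.10 |
| 0.1 | 0.7 | 0.10 | 0.07 | 0 | 0.03 |
| 0.2 | 0.7 | 0.20 | 0.14 | 0 | 0.06 |

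The SD of the change is √(2(1 − r)), which is 1.00 at r = 0.5 and 0.775 at r = 0.7. On the standardised change scale, 0.1–0.2 SD therefore stays 0.1–0.2 at r = 0.5 and becomes 0.13–0.26 at r = 0.7.

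**5. Effect on the test.** Take no true effect, 50 per arm and a shift gone by t1. At r = 0.5 the standard error is 1.00 × √(2/50) = 0.200 for the change score and √(1 − 0.25) × √(2/50) = 0.173 with the covariate. The two-sided false-positive rate rises from 0.05 to 0.08 (s = 0.1) or 0.17 (s = 0.2) for the change score, and to 0.06 or 0.09 with the covariate. Clustering would widen the standard errors and lower these rates, but it would leave the bias in place.

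**6. Direction.** A lower t0 in the AI arm inflates the change-score effect, and a higher t0 shrinks it. The article gives no reason to expect one over the other.

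**7. After re-ordering.** With t0 completed before disclosure, s = 0 in expectation. Every bias above is then 0, and no sample-size figure changes.

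**The case against.** **Disclosure before t0 is not stated.** Assigning a class and telling the class are separate acts, and the blinding statement may mean only that students will notice once they use the tool. A reader might infer that students and teachers definitely know their arm when they sit t0. The article does not say so; it is silent on when they learn it. This stands, and it turns the point from an established bias into a risk left open. It does not remove the point, because the stated order is the weaker one and nothing in the text guards against its consequence.

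**The primary outcome is relatively protected.** It is a competence test, and free-text answers are marked by blinded raters. The route is limited to effort. This stands for H1. The self-rated t0 measures are more exposed, but they are secondary.

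**The size depends on persistence.** Students are still unblinded at t1. An equal effort effect at both time points cancels in the change score, and then only the covariate-adjusted analysis carries a residue. This stands, and both cases are shown in the working.

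**Differential consent.** A reader might infer that the arms will differ in who consents. The documents do not support that. Consent is listed before allocation. The reference to initial sessions may be plural only because there are many seminars. The article appears to describe one form for both randomised conditions. Access to the AI exercises does not depend on taking part, which removes one incentive specific to the AI arm. What remains is that in-person or electronic collection in the first sessions leaves room for late consent after the arm is known.

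**Conclusion.** The point holds as a sequencing weakness that should be corrected. The article puts allocation before baseline, leaves participants unblinded, makes t0 part of the primary outcome, and does not say that the arm is withheld until t0 closes.

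For an assumed t0 shift of 0.1–0.2 SD that does not last to t1, the bias at r = 0.5 is 0.1–0.2 SD in the change score, or 0.05–0.10 SD with baseline as a covariate. The covariate reduces the bias but does not remove it, because it is itself measured after allocation. If the shift persists equally at t1, the change score is unaffected. Both the shift and r are assumptions, and the direction is unknown.

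It would go too far to say that H1 will be biased, or biased in favour of AI: neither disclosure before t0 nor any reaction to it is documented. Late consent after disclosure is a possible secondary risk only. If the trial team already withholds the arm until t0 closes, a sentence saying so settles the baseline point.

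**What to change.** Replace the timeline sentence with this order:
1. Consent.
2. t0, both test and questionnaires.
3. Disclosure of the class's arm to teacher and students by the independent party, once that class's t0 window has closed.
4. Opening of the AI exercises on Stud.IP.

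The instructor balance rule needs one further precaution. With two randomised classes under one instructor in a semester, the possible differences in arm counts are 0 and 2, and only 0 is allowed. Disclosing one arm therefore reveals the other, so both should stay sealed until both t0 windows have closed.

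Record the date of disclosure for each class. Flag any student who consents or completes t0 after it, and repeat the primary analysis without them. This should be a sensitivity analysis, since excluding late students is itself a selection.

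The cost is a revised timeline sentence, a re-ordered start of the course and one extra date per class. The AI exercises may open slightly later; the article gives no schedule from which to say by how much.
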